### Assignment of intervention

#### Sequence generation

The patients will be randomly assigned at the Institut Jules Bordet with a 1:1 allocation as per a computer-generated randomization schedule stratified by institution, HPV status (negative, positive), and lymph node metastasis (no lymph node metastasis or unilateral lymph node metastasis vs bilateral lymph node metastasis).

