#### Implementation

Patients who give consent to participation and fulfil the inclusion criteria will be randomized. For this, Head and Neck Cancer teams will contact the local clinical study coordinator who will schedule the baseline assessment. Randomization will occur after the baseline assessment is completed. The clinical study coordinator is responsible for communicating the allocated group to the clinician who will inform the participant.

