### Study objectives and statistical analyses

The primary goal of this study is to assess and analyze the PROs in terms of swallowing (MDADI) at 6 months after the end of CCRT in subjects randomized to either the pPEG tube group or the rPEG tube group.

The secondary objectives are as follows:Health-related QOL (HRQOL; EORTC QLQ-C30; EORTC QLQ-H&N43 module) and Functional Assessment of Cancer Therapy-Head and Neck (FACT-HN).Dosimetric parameters associated with PROs.CCRT-related toxicities and PEG tube placement complications.The impact of nutritional status on survival and toxicity outcomes.Clinical and radiological tumor response.Loco-regional control (LRC), distant recurrence (DR), second primaries (SP), disease-free survival (DFS), disease-specific survival (DSS), and overall survival (OS). Time to event variable will be assessed from the day of randomization to the day of the first record of any of the considered events.The impact of HPV and tobacco smoking on these secondary endpoints.Cost-effectiveness of each treatment strategy.Clinical validation of cancer prediction models available at www.predictcancer.org.

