### Sample size calculation

The registered subjects are randomized (1:1) between pPEG and rPEG tube placement. The randomization will be stratified by the HPV status and unilateral versus bilateral metastatic neck lymph nodes. The MDADI is a patient-reported outcome scale, and it is composed of 19 items: emotional (6 questions), functional (5 questions), and physical (8 questions) scored from 1 to 5 plus one global question. The mean score of the 19 items will be multiplied by a factor of 20 to obtain a MDADI total score, which ranges from 20 (extremely low functioning) to 100 (high functioning). A difference of 10 points are considered as the minimal clinically important difference (MCID) in the MDADI, as it corresponds to the difference observed between patients taking soft food versus tube feeds [24, 25]. The study’s aim is to detect a difference of at least 10 points between the two arms in the MDADI composite score. Considering an average MDADI composite score of 50 in the prophylactic arm and 60 in the reactive arm (standard deviation 17.5), 100 subjects are needed to detect a significant difference between the two arms (power of 0.80, alpha 0.05 two-sided test). Taking a 10% drop-out rate into account, a total of 110 randomized subjects will be required. To assess survival data, we will use Kaplan-Meier curves with log-rank test. Cox’s proportional hazard model will be used for calculating hazard ratios. To compare continuous outcome variables between the two arms, *t*-test or Wilcoxon test will be used. Categorical variables between the two arms will be analyzed with the chi-square test or Fisher exact test. No data imputation of missing values will be performed. Stratified analyses by HPV status (negative, positive) will be performed as exploratory analyses.

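### The only analysis stated for the 6-month MDADI is an unadjusted t-test or Wilcoxon test; it should be one named model that uses the allocation factors and the baseline score

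*Protocol article*

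**What the plan says.** Under Study objectives and statistical analyses, the primary goal is to "assess and analyze the PROs in terms of swallowing (MDADI) at 6 months after the end of CCRT". The score runs from 20 to 100, so the outcome is handled as continuous.

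Under Sample size calculation, the article assumes means of 50 and 60 with a standard deviation of 17.5 and concludes that "100 subjects are needed to detect a significant difference between the two arms" ("power of 0.80, alpha 0.05 two-sided test"). The difference of 10 points is also taken as the minimal clinically important difference. The same section then gives the analysis methods. For continuous outcomes: "To compare continuous outcome variables between the two arms, *t*-test or Wilcoxon test will be used". No covariate is named. The one analysis that uses an allocation factor is exploratory: "Stratified analyses by HPV status (negative, positive) will be performed as exploratory analyses".

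On allocation, Sequence generation describes a "computer-generated randomization schedule stratified by institution, HPV status (negative, positive), and lymph node metastasis", and Concealment mechanism refers to minimisation. Sample size calculation names HPV and nodal status as stratification factors but not institution. Implementation adds: "Randomization will occur after the baseline assessment is completed".

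**The concern.** Balancing the arms on a prognostic factor removes that factor's contribution to the chance difference between arms. A two-sample test that ignores the factor still counts its variation as noise. The reported standard error is then larger than the true one, the test rejects less often than 5% under the null, and the confidence interval covers more often than 95%.

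The baseline score raises a different issue. Leaving it out does not distort the standard error, but it forgoes precision that the same patients could supply. What is at stake is how tightly the trial can place its estimate against a 10-point threshold, given a sample size with almost no margin over 80% power.

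A second matter is that two tests are named with no rule for choosing between them. The trial is sized on a difference in means, and the Wilcoxon test does not estimate that quantity.

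**Working it through.** **Inputs from the article (Sample size calculation).** Difference 10; SD 17.5; two-sided alpha 0.05; power 0.80; 100 evaluable (50 per arm); 110 randomised with 10% drop-out.

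**Inputs not in the article (assumptions).** R², the share of 6-month MDADI variance explained by the covariates, shown from 0 to 0.25. Collection of MDADI at baseline, which is likely but would be shown in the missing Fig. 2.

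**1. Reproduce the sample size.**
- Normal approximation: n per arm = 2 × (1.96 + 0.8416)² × (17.5/10)² = 48.1, so 49.
- Exact t calculation: 49.05, so 50 per arm and 100 in total. This matches the article.
- Power of the t-test is 80.8% at 100 evaluable. At 110 × 0.9 = 99 evaluable it is 80.4%.

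**2. Effect of ignoring the allocation factors.** The t-test uses SE = 17.5 × √(2/50) = 3.50. If balanced factors explain a share R² of the variance, the true sampling SD is about 3.50 × √(1 − R²). The actual type I error is then about P(|Z| > 1.96/√(1 − R²)).

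| R² of allocation factors (assumed) | True SD of the difference | Type I error | Coverage of the 95% CI |
|---|---|---|---|
| 0 | 3.50 | 5.0% | 95.0% |
| 0.05 | 3.41 | 4.4% | 95.6% |
| 0.10 | 3.32 | 3.9% | 96.1% |
| 0.20 | 3.13 | 2.8% | 97.2% |

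This approximation assumes perfect balance. Simulation with near-balanced strata (6,000 trials per setting, N = 100, four equal strata) gave a type I error of 3.7% at R² 0.10 and 3.3% at R² 0.20, with coverage of 96.0–96.3% and about 97%.

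**3. Effect of ignoring the baseline score only.** In the same simulation, with baseline R² 0.16 and no strata effect, the t-test had a type I error of 5.0% and coverage of 95%. It is valid, with power 80.8% against 86.8% for ANCOVA.

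**4. What ANCOVA would give with 100 evaluable.** Residual SD = 17.5 × √(1 − R²). Half-width = 1.984 × residual SD × √(2/50).

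| Total R² (assumed) | Residual SD | Power | 95% CI half-width (points) |
|---|---|---|---|
| 0 | 17.50 | 80.8% (80.3% simulated, with the covariates fitted) | 6.95 |
| 0.10 | 16.60 | 84.7% | 6.59 |
| 0.16 | 16.04 | 87.0% | 6.37 |
| 0.25 | 15.16 | 90.4% | 6.02 |

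Simulated comparisons agree. With strata R² 0.10, power was 81.4% for the t-test and 84.3% for ANCOVA. With strata R² 0.10 plus baseline R² 0.16, it was 81.7% and 90.3%.

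**5. The open choice of test.** The article's effect size is a difference in means, 60 − 50 = 10. A t-test or ANCOVA estimates that difference with an interval. The Wilcoxon test compares the two distributions by ranks and yields no estimate of the mean difference.

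**The case against.** The strongest reply is that the plan is right by its own figures. The sample size reproduces, the planned t-test reaches the stated power, and any distortion is conservative. That stands: this is a loss of efficiency, not an error in the sizing or a threat of false positives.

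A second reply is that the sentence covers continuous outcomes in general, in a condensed article, and a separate SAP may specify a model. That is possible. But the article does state a method, it is the only one that applies to the primary outcome, and it is unadjusted, so the text needs changing or aligning in either case.

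Third, the gain depends on R², which the article does not give. It is nil if the covariates do not predict the score. The exclusion of patients with grade 2 or worse dysphagia probably narrows the range of baseline scores and could weaken their correlation with the 6-month score. This also stands, and is why the results are shown as a range starting at zero.

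Some stronger readings are tempting but not supported:
- A reader might infer that the Wilcoxon option leaves the trial underpowered, since it gives about 78.5% at 99 evaluable. That figure assumes normal data, where the t-test would be the natural choice. With a skewed, bounded score the Wilcoxon test can match or exceed the t-test.
- A reader might infer that HPV adjustment has been demoted to exploratory. The sentence on HPV-stratified analyses reads as subgroup analysis, for which exploratory status is appropriate.
- A reader might extend the remedy to the video fluoroscopic examination. The article states no score for it, so there is nothing to model.

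**Conclusion.** The point holds as a matter of efficiency and pre-specification. The article fixes an unadjusted comparison for a primary outcome whose allocation is balanced on factors known for every patient, and it leaves two tests open.

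If HPV and nodal status predict MDADI, the t-test is conservative, with a type I error of roughly 3% to 4.5% for assumed R² of 0.05 to 0.20. Only this omission makes the interval too wide in the strict sense; omitting the baseline score costs precision alone. Relative to the planned 80.8%, ANCOVA would gain about 4, 6 or 10 percentage points of power at R² 0.10, 0.16 or 0.25, and would lose under 1 point at R² 0.

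It would be wrong to conclude that the trial misses its stated power or that its result would be invalid. The direction of the effect is secure; its size rests on assumed R² values and, for the larger gains, on baseline MDADI being collected. The change is worth making because the possible gain far exceeds the possible loss.

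**What to change.** Name one primary analysis: ANCOVA of the 6-month MDADI composite on arm, HPV status, nodal status and, if collected, baseline MDADI. Report the adjusted mean difference with its 95% CI against the 10-point difference. Keep the t-test or Wilcoxon test as a sensitivity analysis.

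Before institution enters the model, reconcile Sequence generation, which lists it as a stratification factor, with Sample size calculation, which does not. Add it if it is an allocation factor.

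The same approach can be used for the continuous health-related quality-of-life scores. If an SAP already specifies such a model, align the protocol text with it.

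The cost is one sentence and a few degrees of freedom, with no additional patients and no new data.

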### Toxicity evaluation

A clinical assessment will be performed weekly, during the radiation therapy and at 1, 3, 6, 12, 24, and 36 months after the treatment. Concurrently, patients will pursue the standard follow-up visits: every 2–3 months for the first 2 years, every 3–6 months in 3rd, 4th, and 5th years and then yearly further on. Toxicity is defined as acute when occurring during RT and/or in the 3 months after the end of RT and as late from then on. Intensity of all adverse events will be graded by a specialized head and neck radiation oncologist using the National Cancer Institute (NCI)–CTCAE version 5.0 on a 5-point scale (grades 1 to 5) and the RTOG/EORTC grading scale [32].

As an objective evaluation of dysphagia, a video fluoroscopic swallowing examination (VFSE) will be performed at baseline, 3, 6, 12, and 24 months after the treatment. A salivary test analyzing saliva quantity and quality will evaluate xerostomia at defined study time points illustrated in Fig. 1.

All serious adverse events (SAEs) related to a protocol-mandated intervention will be reported on SAE for and transmitted to the EudraVigilance Clinical Trial Module, the Competent Authorities, the Ethics Committees, and the participating investigators.

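### Toxicity is recorded as ordered grades, but the only tests named for categorical outcomes ignore order; if grades are compared across levels, power against a one-directional shift is lost

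*Protocol article*

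**What the plan says.** Three places in the protocol article bear on this.

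- **Study objectives and statistical analyses** lists as a secondary objective "CCRT-related toxicities and PEG tube placement complications". It names no summary measure, cut-point or time window for comparing the arms.
- **Toxicity evaluation** says how events are graded: CTCAE version 5.0 "on a 5-point scale (grades 1 to 5) and the RTOG/EORTC grading scale". It separates acute toxicity (during radiotherapy and up to 3 months after it) from late toxicity.
- **Sample size calculation** holds the test rules. For categorical outcomes: "Categorical variables between the two arms will be analyzed with the chi-square test or Fisher exact test". For continuous outcomes: "To compare continuous outcome variables between the two arms, *t*-test or Wilcoxon test will be used". No trend, rank or ordinal method is named for ordered categories.

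**The concern.** A toxicity grade is neither continuous nor a set of unordered labels. Taken literally, the two rules send it to chi-square or Fisher. On a grade-by-arm table, those tests give the same p-value however the grades are permuted, so a steady drift to worse grades in one arm earns no more credit than irregular scatter of the same size. The full-table test also gives no direction and no effect estimate.

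What is at stake is efficiency and interpretation. With 110 patients randomised, toxicity comparisons will be imprecise anyway. A real shift in, say, mucositis or dysphagia grade could more easily come out non-significant and be read as no difference between prophylactic and reactive placement.

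**Working it through.** **1. The plan's own figure.** The article states: "Considering an average MDADI composite score of 50 in the prophylactic arm and 60 in the reactive arm (standard deviation 17.5), 100 subjects are needed" ("power of 0.80, alpha 0.05 two-sided test"). By the normal approximation, n per arm = 2 × (1.960 + 0.842)² × 17.5² / 10² = 2 × 7.85 × 3.0625 = 48.1, so 49 per arm. The t-test solution is 49.05, so 50 per arm and 100 in total. Adding 10% gives 100 × 1.10 = 110, as stated. Power of the t-test at 50 per arm is 0.808. This figure reproduces and concerns the MDADI only. No power or effect size is stated for toxicity.

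**2. Why order matters.** Suppose a one-directional shift carries a noncentrality of 7.85, which gives 80% power on 1 degree of freedom (a rank or trend test). As an idealised case, spread the same signal over the degrees of freedom of an unordered table (number of categories minus 1), at two-sided 0.05:

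| Categories | df | Power |
|---|---|---|
| trend test | 1 | 0.80 |
| 3 | 2 | 0.71 |
| 4 | 3 | 0.64 |
| 5 | 4 | 0.60 |

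The loss grows with the number of occupied categories.

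**3. Simulation, latent shift.** Inputs: 50 per arm; two-sided 0.05; 20,000 replicates (simulation standard error at most √(0.25/20,000) = 0.0035). The control-arm grade distributions are assumed. So is the shift of 10/17.5 = 0.571 SD, which is borrowed from the MDADI because the article has none for toxicity.

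| Assumed control distribution (%) | Wilcoxon | Chi-square, full table | Difference |
|---|---|---|---|
| 10/25/35/25/5 | 0.759 | 0.528 | 0.231 |
| 20 in each of five | 0.756 | 0.537 | 0.219 |
| 30/35/20/12/3 | 0.758 | 0.532 | 0.226 |
| 20/40/30/10 | 0.753 | 0.582 | 0.171 |

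Under the null, rejection rates were 0.048–0.051 (Wilcoxon) and 0.043–0.051 (chi-square), so both tests are valid. A repeat run agreed to within about 0.01. With three occupied grades the gap at this shift is about 9 to 12 points.

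**4. Simulation, proportional-odds shift.** 50 and 55 per arm, again with assumed distributions. Loss of full-table chi-square against Wilcoxon, in percentage points:

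| Occupied categories | OR 1.5 | OR 2 to 3 |
|---|---|---|
| five | 8–10 | 17–24 |
| four | 7 | 13–18 |
| three | 4–5 | 8–11 |
| two | 0 | 0 |

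The two-category row compares both tests on data already collapsed to yes/no, where they coincide.

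**5. Collapsing to a single cut.** Set against the rank test on the full grade, the best cut in each distribution lost about 2 to 14 points across the runs. For example, with 10/25/35/25/5 and OR 3, Wilcoxon had 0.854 and a cut after the second category 0.793. Poorly placed cuts lost much more: in the latent-shift runs their power was 0.25–0.58, against 0.75–0.76 for Wilcoxon.

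**6. Non-monotone differences.** Here the ranking reverses. For 20% in each category against 10/30/20/30/10, chi-square had 0.42 and Wilcoxon 0.05. For 10/30/40/15/5 against 20/30/20/20/10, the figures were 0.48 and 0.07.

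Fisher's exact test on the full table was not simulated; it also ignores order. No run used six occupied categories.

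**The case against.** The strongest reply is that the article never says toxicity will be tested as an unordered five-level table. The sentence on categorical variables is generic and does not mention toxicity. The comparison could be a complication yes/no, an incidence or a grade 3 or higher rate, and for those chi-square or Fisher is the right kind of test. The choice of worst grade, window and cut-point is normal analysis-plan content, and this is a condensed article. That stands, and it is why the point is conditional on grades being compared across levels. What remains is that the article does state a rule, and that rule restricts Wilcoxon to continuous outcomes. An analysis plan that follows it would inherit the problem.

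A reader might also infer that the plan simply loses 17 to 23 points of power, the range in the latent-shift table. The documents do not support that as a fact. They give no grade frequencies and no toxicity effect, the 0.571 SD belongs to the MDADI, and a monotone shift favours a rank test by construction. The loss shrinks with fewer occupied grades and reverses for non-monotone patterns. Against this, whether one strategy is more toxic than the other is a directional question, so a monotone alternative is the natural one to target.

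Nor does it follow that a grade 3 or higher rate should be reduced to a descriptive figure. A severe-toxicity proportion answers a different clinical question from an average shift across grades, and testing it is legitimate.

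**Conclusion.** The concern holds in conditional form. As written, ordered toxicity grades fall under a rule that ignores their order. If they are compared across levels under that rule, the result is valid but less powerful against a one-directional shift. With 50 to 55 per arm and a monotone shift of about 0.57 SD or an odds ratio of 2 to 3, the loss is about 13 to 24 points with four or five occupied grades and about 8 to 12 with three. These sizes rest wholly on assumed grade distributions and effects. At an odds ratio of 1.5 the loss is 4 to 10 points.

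This is not an error in type I control, and it does not touch the MDADI analysis or the sample size. It is a low-cost gain for a secondary objective that was never powered.

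**What to change.** Amend the test rules under Sample size calculation so that ordered outcomes, for example the worst CTCAE and RTOG/EORTC grade per toxicity in the acute and in the late period, with no event as the lowest category, are compared between arms by the tie-corrected Wilcoxon rank-sum test or by a proportional-odds model reporting a common odds ratio with 95% CI. Keep chi-square or Fisher for binary and unordered variables, including a grade 3 or higher rate and PEG complication yes/no.

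The cost is one sentence and slightly different code. Wilcoxon is already in the plan, and no data, patients or procedures change. The small downside is that a common odds ratio averages across grades and is less familiar to clinicians than a percentage; the grade 3 or higher rate beside it covers that.

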**Drop out criteria**	
• Refusal to participate	

*ECOG* Eastern Cooperative Oncology Group, *GLIM* Global Leadership Initiative on Malnutrition, *CTCAE* Common Terminology Criteria for Adverse Events

^a^HPV tumor status testing is performed by surrogate marker p16 immunohistochemistry either on the primary tumor or from cervical nodal metastases. The threshold for positivity is at least 70% nuclear and cytoplasmic expression with at least moderate to strong intensity [27]. Additional HPV-specific testing are permitted for the protocol

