#### Patient-reported outcomes

PROs will be measured at different time points of the study via the questionnaires illustrated in Fig. 2. They will be completed at the hospital before the clinical examination, using CANKADO software, class I medical device, within the European Union (registration number DE/CA59/11976/2017) version 1.6 30-DEC-2020, installed on an electronic portable device. A paper version of the questionnaires will be proposed to any patient unfamiliar with electronic devices.

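### The primary 6-month MDADI comparison is confined to patients with an observed 6-month score, and would be biased if loss depends on swallowing and differs by arm

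*Protocol article*

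**What the plan says.** Under Study objectives and statistical analyses, the primary goal is to "assess and analyze the PROs in terms of swallowing (MDADI) at 6 months after the end of CCRT", which is a single visit. The Sample size calculation section holds the analysis rules. Continuous outcomes are compared between arms by t-test or Wilcoxon test, and "No data imputation of missing values will be performed". No other method is named for a continuous outcome.

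The same section plans on "an average MDADI composite score of 50 in the prophylactic arm and 60 in the reactive arm" ("standard deviation 17.5"; "power of 0.80, alpha 0.05 two-sided test"), which gives 100 evaluable patients. It then adds: "Taking a 10% drop-out rate into account, a total of 110 randomized subjects will be required".

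The Patient-reported outcomes section says that questionnaires are given at several time points and filled in at the hospital before the clinical examination. The schedule itself is in Fig. 2, which is not available in the text reviewed. Under Implementation, participants are told their allocated group.

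**The concern.** Not imputing does not by itself force a complete-case analysis, because a likelihood-based repeated-measures model uses partial data without imputing anything. The restriction comes from pairing that rule with a test on one visit: a patient without a 6-month score contributes nothing, whatever was recorded at other visits.

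That is harmless if loss is unrelated to swallowing. There are reasons to doubt it here. Completion depends on attending hospital, so sicker patients are likelier to be missing. Patients know their arm. The article's Discussion expects the arms to differ in nutrition, oral feeding and late dysphagia, so loss could differ in amount or in kind between them. The difference among attenders could then be too small or too large. Randomising more patients would not correct it.

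**Working it through.** **1. The plan's own figures.** Difference 10, SD 17.5, two-sided alpha 0.05, power 0.80, all from Sample size calculation.

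- Normal approximation: n per arm = 2 × (1.960 + 0.842)² × 17.5² / 10² = 48.07, so 49 per arm or 98 in total.
- Exact t-test power: 0.7996 with 49 per arm and 0.8076 with 50 per arm. The stated 100 reproduces.
- Inflation: 100 × 1.10 = 110. Dividing instead, 100 / 0.90 = 111.1, gives 112. The stated 110 is close enough.
- If exactly 10% of 110 are lost, 99 remain and t-test power is 0.804.

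**2. Bias in the observed-case difference.** The document gives no loss pattern, so these inputs are assumptions:

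- the true 6-month difference (reactive minus prophylactic) is 10 and the SD is 17.5;
- an earlier score has correlation 0.7 with the 6-month score;
- the log-odds of loss rise by b for each SD that the earlier score is lower, with b from 0.5 to 1.5.

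Write Z for the standardised earlier score. An arm's observed-case mean exceeds its true mean by 0.7 × 17.5 × E(Z | retained) = 12.25 × E(Z | retained). Numerical integration gives this upward shift, in points:

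| b | 9% lost | 10% lost | 20% lost | 25% lost |
|---|---|---|---|---|
| 0.5 | 0.54 | 0.60 | 1.18 | 1.46 |
| 1.0 | 1.01 | 1.11 | 2.12 | 2.61 |
| 1.5 | 1.36 | 1.49 | 2.78 | 3.39 |

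The observed-case difference is 10 + (reactive shift) − (prophylactic shift).

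- **10% in each arm, same b:** the shifts cancel, giving 10.0.
- **10% in total, one common mechanism, arms also 10 points apart at the earlier visit:** loss is then slightly higher in the lower-scoring arm (12.3% vs 7.7% at b = 1.0). The difference is 9.9, 9.5 and 9.2 for b = 0.5, 1.0 and 1.5, so the bias is under 1 point.
- **25% prophylactic vs 9% reactive, same b:** 10 + 0.54 − 1.46 = 9.08; 10 + 1.01 − 2.61 = 8.40; 10 + 1.36 − 3.39 = 7.97. The bias is about 1 to 2 points.
- **10% prophylactic vs 20% reactive, same b:** 10 + 1.18 − 0.60 = 10.58; 10 + 2.12 − 1.11 = 11.01; 10 + 2.78 − 1.49 = 11.29. The direction reverses.
- **Loss related to the score in the prophylactic arm only:** at 10% vs 10%, 10 − 0.60 = 9.40 down to 10 − 1.49 = 8.51. At 25% vs 9%, 10 − 1.46 = 8.54 down to 10 − 3.39 = 6.61.

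**3. Loss driven by the unseen 6-month score itself.** With one common mechanism, 10% total loss and b = 0.5 to 1.0, a simulation with 400,000 per arm gave 9.86 and 9.38. Its control run without selection gave 10.06, so simulation error is of the order of 0.06.

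**The case against.** The strongest reply is that nothing in the document shows the harmful pattern. The plan expects 10% loss. At that level, with one mechanism in both arms, the bias is under 1 point against a 10-point target, and the larger figures need loss well beyond the plan or selection in one arm only. That is correct, and it limits the size of the point. It does not remove the point: the analysis rule is stated, and it discards scores that the trial collects.

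A second reply is that a statistical analysis plan may add sensitivity analyses. It may, but it would have to depart from a flat published sentence to do so.

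A third is that a mixed model recovers the true difference fully only when loss depends on scores it has seen. That also stands. Under loss driven by the missing score itself, recovery is only partial, which is why a sensitivity analysis is needed.

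Three stronger readings are tempting, and the document does not support them:

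- **That the trial is underpowered.** t-test power falls below 0.80 once about 11% are lost, but this restates the plan's own allowance. No higher loss is predicted anywhere. With Wilcoxon (assumed relative efficiency 0.955) the margin is nearer 6%, and power at 10% loss is 0.785, a small shortfall.
- **That patients who decline their allocated tube strategy leave the analysis.** Table 1 lists "Refusal to participate" as the only drop-out criterion. It does not say that such patients leave follow-up or the analysis. So short a list can equally mean that toxicity or crossover does not end participation.
- **That one blank item voids a form.** The article describes a mean of 19 items but no such rule. Electronic completion is the default: "A paper version of the questionnaires will be proposed to any patient unfamiliar with electronic devices". Item scoring is usually left to the full protocol or analysis plan.

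**Conclusion.** The concern holds in a limited form. As written, the primary result is an observed-case comparison at one visit that ignores the patients' other MDADI scores. It is biased only if loss is related to swallowing and differs by arm in amount or in kind. The document makes that plausible but gives no evidence of it.

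Under the assumptions above, the error is under 1 point at about 10% total loss with a common mechanism and about 1 to 2 points at 25% versus 9%. It reaches about 3.4 points (10 − 6.61) only if strong selection acts in one arm alone at those unequal rates. The direction depends on which arm loses more. The figures of 100 and 110 patients and the stated power stand. The change is worth making because it is cheap and uses data already being collected.

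**What to change.** Make the primary analysis a likelihood-based mixed model for repeated measures on all scheduled MDADI scores, including baseline. Include arm-by-visit and baseline-by-visit terms and the stratification factors, analyse patients as randomised, and name the 6-month contrast as primary. This model needs no imputation.

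Add one delta-adjusted sensitivity analysis for data missing not at random. Since that is commonly done by imputation, narrow the no-imputation sentence so that it does not forbid it. Keep the observed-case t-test as supportive.

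If Fig. 2 schedules no MDADI between baseline and 6 months, use a baseline-adjusted model of the 6-month score instead. It would recover less, because only baseline would inform the missing values.

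The cost is revised wording and some programming. The primary result would then rest on a missing-at-random assumption, which the sensitivity analysis tests. Neither option asks for an assessment beyond the existing schedule.
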